### Sample size and justification for power calculations

In conducting power calculations, we considered assessment attrition, within-clinician correlation, and within-setting effects. Based on a power curve calculation with the following assumptions: 30 clinicians per condition; 4 sessions rated for fidelity per clinician, randomly selected over time; with an alpha-level of 0.05, within provider correlation estimated at 0.38, 10% proportion of variance accounted for by the random effect associated with agency, based on a two-sided test, the detectable effect size for at least 80% power will be medium to large, per Cohen’s [68] classifications, ranging from d = 0.41 to 0.55.

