### Trial status

To date, six workshops have been completed, and, through efforts to enroll clinicians over three waves of recruitment, the recruitment goal of 90 clinicians was exceeded. The first and second waves of consultation have been completed, and the third wave is underway. Pre- and post-training interviews with providers from waves one and two are complete. Thus far, our retention rate and compliance with study procedures (*e.g*., uploading of sessions) has been high, and a high proportion of clinicians uploaded recordings at baseline and over the course of the consultation period. We anticipate that data collection will be complete in early 2014.

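### The lower end of the stated detectable range, d = 0.41, cannot be reached from the printed inputs when any two of the three conditions are compared, and the range is around medium, not medium to large

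*Protocol article*

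**What the plan says.** The section on sample size and power calculations in the protocol article prints a nearly complete set of inputs: "30 clinicians per condition", "4 sessions rated for fidelity per clinician", "with an alpha-level of 0.05", "within provider correlation estimated at 0.38, 10% proportion of variance accounted for by the random effect associated with agency", and "based on a two-sided test". From these it concludes that "the detectable effect size for at least 80% power will be medium to large" on Cohen's scale, "ranging from d = 0.41 to 0.55".

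The paragraph does not say which contrast the range refers to, what varies between its two ends, or whether the agency share lies inside the 0.38 or is added to it. Attrition is listed among the things considered, without a rate. The Trial status section reports that "the recruitment goal of 90 clinicians was exceeded".

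Hypothesis 1 orders the three conditions: technology-enhanced consultation highest, standard consultation in the middle, no consultation lowest.

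**The concern.** This is the article's only statement of what the trial can detect on its primary outcome, and its result can be checked against its own inputs. An ordering of three conditions has to be shown by comparing conditions with each other, 30 clinicians against 30. If the design does not have 80% power at 0.41 for such a comparison, the favourable end of the range overstates its sensitivity. The comparison most exposed is enhanced against standard consultation. A reader who sees no difference there could conclude that effects of about 0.4 were likely to have been found, when power at that size is not far above one half. The label pushes the other way, since it describes a range around medium as reaching towards large.

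**Working it through.** **Inputs from the sample-size section.** n = 30 per condition, m = 4 sessions, within-provider correlation ρ = 0.38, agency share 0.10, two-sided α = 0.05, power 80%. I assume that any two sessions of one clinician are equally correlated, and that d is in units of the total session-level standard deviation.

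**Formula.** With total variance 1, the mean of four sessions has variance v = ρ + (1 − ρ)/4. The detectable difference is d = (1.960 + 0.842) × √[v(1/n₁ + 1/n₂)] = 2.802 × √[v(1/n₁ + 1/n₂)]. The t figures solve the same problem with the noncentral t distribution.

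**Plain reading, 30 v 30.** v = 0.38 + 0.62/4 = 0.535, so d = 2.802 × √(2 × 0.535/30) = 0.529 (t: 0.538). This lies inside the stated range.

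**All readings of the agency share**

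| Agency share | v | d, 30 v 30: normal / t | Power at 0.41: normal / t | n per arm for 80% at 0.41 (normal) | d, 60 v 30: normal |
|---|---|---|---|---|---|
| Inside the 0.38, removed: 0.28 + 0.62/4 | 0.435 | 0.477 / 0.485 | 67% / 66% | 41 | 0.413 |
| Removed from the total: 0.9 × 0.535 | 0.4815 | 0.502 / 0.510 | 63% / 61% | 45 | 0.435 |
| Separate, removed: 0.38 + 0.52/4 | 0.510 | 0.517 / 0.525 | 60% / 59% | 48 | 0.447 |
| Ignored: 0.38 + 0.62/4 | 0.535 | 0.529 / 0.538 | 58% / 57% | 50 | 0.458 |
| ρ = 0.10 + 0.9 × 0.38 = 0.442 | 0.5815 | 0.552 / 0.561 | 55% / 53% | 55 | 0.478 |
| Added: ρ = 0.48 | 0.610 | 0.565 / 0.575 | 53% / 52% | 57 | 0.489 |

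**Upper end.** At d = 0.55, 30 v 30, normal-approximation power is 83.0% with ρ = 0.38 and 79.8% with ρ = 0.442. With 28 per arm and ρ = 0.38 the detectable d is 0.548. So 0.55 reproduces.

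**Lower end.** No row gives a 30 v 30 value below 0.477. Solving for 0.41 gives v = (0.41/2.802)² × 15 = 0.321, hence ρ = (4 × 0.321 − 1)/3 ≈ 0.095, against the printed 0.38. At the printed correlation, 80% power needs 41 to 57 per arm, or 123 to 171 clinicians over three arms, against a goal of 90.

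**Where 0.41 can come from.** With both consultation arms pooled (60 v 30) and the agency share inside the 0.38 and removed: 2.802 × √[0.435 × (1/60 + 1/30)] = 0.413. The other readings of agency give 0.435 to 0.489 for that contrast.

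**Label.** With 0.5 as medium and 0.8 as large (assumed; the article cites the scale but does not print it), 0.41 is 0.09 below medium and 0.55 is 0.05 above it. Large is 0.25 above the upper end.

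**Attrition (secondary).** The goal of 90 equals 3 × 30, so each clinician lost below that goal reduces the number on which the power was calculated. Under an assumed 10% loss (27 per arm) the pairwise d is 0.512 to 0.607 (t) over the readings above. Under 20% (24 per arm) it is 0.545 to 0.645.

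**The case against.** The strongest defence is that 0.41 belongs to a comparison the article does describe. The abstract asks whether clinicians with post-workshop support do better than those without it, and the Background says that the two consultation conditions are set against no consultation to measure the added benefit. Pooled in this way, 0.413 is attainable. Pairing that figure with a 30 v 30 comparison after 20% loss, under the same agency reading (0.545 by t), gives almost exactly 0.41 to 0.55. This stands as a possible origin. It needs a contrast, a loss rate and an agency treatment that the power paragraph does not state, and it concedes that 0.41 is not a figure for two conditions.

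A second defence is that sessions are sampled over time, so correlation may decay. If 0.38 were the correlation of adjacent sessions under AR(1), the 30 v 30 value would be 0.477, or 0.419 with agency also removed. That comes close to 0.41 without reaching it, and the paragraph states no decay.

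A reader might go further and infer that the whole range fails, or that no attrition allowance was made. The document supports neither. The upper end reproduces, and the plain pairwise value of 0.53 to 0.54 lies inside the range. The value 0.55 also fits a loss of about 7% (28 per arm), so a small allowance cannot be excluded. An unprinted loss rate is normal in a condensed article, and the goal of 90 was exceeded by an unstated number.

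It is also fair that recruitment is finished and that the label stands beside explicit numbers. Both limit the harm.

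**Conclusion.** The point holds for the lower bound and the label, and no further. On the printed inputs with equal correlation between sessions, a comparison of two conditions has 80% power at d of about 0.48 to 0.57 (normal) or 0.49 to 0.58 (t). At 0.41 its power is 52 to 66% by t. The 0.41 is attainable only for pooled consultation against none under the most favourable agency reading, and that contrast cannot test enhanced against standard consultation, which Hypothesis 1 requires. The upper bound of 0.55 stands.

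The label finding depends on the assumed benchmarks of 0.5 and 0.8. The attrition figures depend on assumed loss rates; they show sensitivity and are not evidence of an error. No endpoint, analysis or enrolment decision is affected. What changes is how a null pairwise result may be read.

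**What to change.** Rewrite the sentence that gives the range so that it:

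- states the detectable effect for a single pairwise contrast as about d = 0.49 to 0.58 at 80% power with complete data, or as one value once the agency treatment is fixed;
- says whether the 10% agency share is inside the 0.38, and whether the model removes it;
- labels 0.41 as the pooled-consultation contrast if that is its source, and otherwise deletes it;
- calls the effect medium.

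Add a sensitivity range for clinician loss, marked as an assumption: about 0.51 to 0.65 for 10 to 20% loss. If the sponsor holds the rate that was used, print that rate and its result instead.

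The cost is a rewritten sentence or two and a less favourable stated sensitivity. Enrolment, data collection and the planned analyses stay as they are.

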### Recruitment and randomization

We recruited OSI clinicians directly. Recruitment took place at CPT workshops in Canada from 2012 to 2013. Three months before the first workshop, the OSINN invited clinicians and clinic coordinators from the OSI clinic network, Canadian Forces health services, and approximately 800 community-based clinicians who provide services to veterans with PTSD. The clinicians include psychologists, social workers, psychiatric nurses, and psychiatrists. This invitation was accompanied by a letter soliciting participation in the study. Prior to enrolling clinicians, ethics approval for the study was obtained from the clinic or institution where the clinician worked. Community clinicians were informed that the CHIR-supported workshop was free, and 24 clinicians received up to $500 reimbursing travel and accommodation. Partial reimbursement for the community clinicians was intended to offset the barrier of cost associated with a two-day workshop. Following the initial CIHR-funded workshop, two provincial health authorities and one hospital hosted workshops. One of the authors ([name]) was the primary CPT trainer. Interested clinicians consented prior to, or within the week following the workshop. Consent forms outlined the purpose and requirements of the study, as well as potential risks. A random allotment of participants was generated by the study statistician for each condition. To avoid any biases in condition assignment, condition assignment was communicated by participant number to the study coordinator after participant numbers had been assigned to the consented participants. Clinicians received a notification e-mail from the study coordinator within one week after the workshop regarding their randomized condition. The e-mail also included consultant contact information and a schedule of consultation sessions (if applicable to their condition). As in other studies of this nature (e.g., [52]), the clinicians were asked to provide an information sheet about the study and obtain verbal consent from patients who agreed to participate in the study, then document patient consent in his/her medical records. Upon returning to their respective work places, participants began audio-recording CPT sessions with consented patients.

### Proposed analytic strategy

Trial reporting will follow the CONSORT 2010 statement for reporting randomized controlled trials [69]. Analyses will be preceded by careful examination of the descriptive statistics and distributional form of all variables. The effectiveness of randomization will be evaluated by comparing the different conditions on baseline measures, demographics, and key outcome variables using Chi-squared tests and t-tests. The primary analyses will be conducted using random effects regression modeling. These models provide more flexibility in modeling missing data than general linear models and are appropriate for nested data. ‘Intention-to-train’ principles will be used in the analyses of clinicians who are assigned to a consultation modality but either fail to engage or are unable to fulfill the post-workshop participation requirements (*e.g*., do not attend consultation sessions). Analyses of both the intention-to-train and completer samples will be conducted.

To explore the contribution of organization and clinician-level factors to the outcomes of interest, in addition to random effects regression modeling, we will conduct qualitative analyses on interview data. Qualitative and quantitative data will be integrated to facilitate a fine-grained understanding of processes and characteristics that influence training outcomes. Interviews will be analyzed in line with goals, objectives and key research questions. Using content analysis, we will identify analytical categories to describe and explain our observations. Our work will occur in five stages outlined in Pope, Ziebland, and Mays’ framework approach to qualitative analysis [70]: Familiarization; Identifying a Thematic Framework; Indexing; Charting; and Mapping and Interpretation. In the second stage, codes will be derived deductively by identifying categories at the beginning of the research (*e.g*., elements of the CFIR), and inductively by identifying those that emerge gradually from the data. In subsequent phases, survey data on contextual factors will be examined in conjunction with fidelity scores for the purposes of validation, hypothesis generation, and expansion [71,72] to understand ways in which contextual factors influence fidelity to CPT.

### Trial status

To date, six workshops have been completed, and, through efforts to enroll clinicians over three waves of recruitment, the recruitment goal of 90 clinicians was exceeded. The first and second waves of consultation have been completed, and the third wave is underway. Pre- and post-training interviews with providers from waves one and two are complete. Thus far, our retention rate and compliance with study procedures (*e.g*., uploading of sessions) has been high, and a high proportion of clinicians uploaded recordings at baseline and over the course of the consultation period. We anticipate that data collection will be complete in early 2014.

## Discussion

There are four significant innovations that the current project offers the field of Implementation Science. First, this will be the first study to examine psychotherapy training and consultation within a broader implementation context. Previous randomized training studies have not examined the organizational context. Our use of mixed-methods research strategies in the context of a randomized controlled trial [72] will allow us to examine a broad range of potential influences on the outcomes that we are assessing. This approach will extend our understanding of interactions between these factors and training outcomes.

A second major advancement is the empirical investigation of the optimal (efficacious, scalable and replicable) methods of post-workshop consultation. To adequately test the incremental value of consultation, we are conducting a randomized, dismantling research design, which includes manipulation of the type of post-workshop consultation while holding other variables constant. Results will help inform policy on post-workshop support. The inclusion of the fidelity monitoring only condition allows for testing an as yet unevaluated and potentially efficient strategy for increasing fidelity to EBPs: recording sessions with the knowledge that they will be reviewed and evaluated for fidelity. Our control condition allows for the formal testing of this possibility while allowing us to examine the incremental value of different types of expert consultation.

Although fidelity is a key implementation outcome in the model by Proctor and colleagues [73] and in this study, fidelity to EBPs has not been adequately assessed by independent evaluators in prior implementation research. It has either not been assessed at all, or has been assessed through self-report, standardized patient protocols [74], or a single session selected by providers (c.f., [52,75]). Our third innovation is to improve upon this methodological limitation of prior studies by randomly selecting audio-recorded sessions for fidelity monitoring. We will also conduct the only investigation of the effect of clinician fidelity to an EBP in routine care settings on PTSD outcomes to date. Because this investigation will examine sessions from novice clinicians who received varying intensities of consultation, we expect to see a greater range of fidelity than that seen in previous investigations of the impact of fidelity on symptom outcomes, as most studies to date have used clinical trial data with sessions from closely supervised clinicians. Finally, no evidence-based guidance exists regarding how to facilitate fidelity to the CPT protocol and ultimately patient outcomes. Using transcripts from consultation sessions, members of our research team will develop and test a theory of evidence-based consultation.

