**Methods:**

The current study investigates whether clinicians receiving post-workshop support (six-month duration) will deliver CPT with greater fidelity (*i.e*., psychotherapy adherence and competence) and have improved patient outcomes compared with clinicians receiving no formal post-workshop support. The study conditions are: technology-enhanced group tele-consultation; standard group tele-consultation; and fidelity assessment with no consultation. The primary outcome is independent assessment (via audio-recordings) of the clinicians’ adherence and competence in delivering CPT. The secondary outcome is observed changes in patient symptoms during and following treatment as a function of clinician fidelity. Post-consultation interviews with clinicians will help identify facilitators and barriers to psychotherapy skill acquisition. The study results will inform how best to implement and transfer evidence-based psychotherapy (*e.g*., CPT) to clinical settings to attain comparable outcomes to those observed in research settings.

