## Methods

This randomized controlled dismantling trial has independent fidelity rating as the primary outcome and patient outcomes as the secondary outcomes. Clinicians are randomly assigned to six months of post-workshop support following an intensive two-day CPT workshop delivered by the last author. The conditions are: standard group tele-consultation, technology-enhanced group tele-consultation, or no consultation/fidelity monitoring only. The post-workshop consultation conditions vary as to whether audio-recorded therapy sessions and other work samples, such as CPT worksheets, are reviewed in the group. This design permits the evaluation of the additive value of each of the elements (*i.e*., expert consultation, technology-assisted expert consultation). Follow-up assessments of fidelity will be conducted at six months post-workshop for clinicians, and follow-up symptom assessments will be conducted at three months post-treatment for patients.

Participation in the study requires that all clinicians consent at least two clients to have all of their CPT sessions audio-recorded for use in consultation and/or fidelity rating. Four therapy sessions will be randomly selected across the six-month period for fidelity rating, and fidelity to treatment will be assessed by trained graduate students and post-doctoral fidelity assessors. Consistent with recommended clinical practice and research trials, patient outcomes will be assessed pre-treatment, at alternate therapy sessions, and at three months post-treatment. A secure web-based application is used to manage the continuous uploading of encrypted audio-recorded therapy sessions to the study server and to protect the privacy and confidentiality of patients and clinicians. Study-provided digital audio-recorders (USB-equipped) are used to record, store and upload CPT sessions to the secure server for fidelity ratings. Study staff retrieve the randomly-selected audio-recordings and assign them to the CPT fidelity raters, who are blinded to study condition. To check if rater blinding has been achieved, fidelity raters will be asked to guess the study condition for each session they rated. Patient self-report data is collected by the clinicians, who then upload the data directly to the server and clinician CPT activity outside of study-related procedures is also recorded.

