### Interventions

Participants in all conditions attend the workshop, receive the CPT manual and related materials, and have access to resources available through the free CPT-web online training (https://cpt.musc.edu/index). All participants who upload the required number of session recordings and patient symptom measures will be eligible to receive ‘CPT Provider’ status. This status is not tied to any change in remuneration for services. Provider status will be awarded to clinicians who demonstrate an acceptable level of fidelity to CPT based on session recordings randomly selected from the last two weeks of the six-month post-workshop period. Workshop participants who provide informed consent are randomized to one of the three post-workshop consultation conditions after completing the workshop. Participants in the two tele-consultation conditions receive six months of weekly one-hour group tele-consultation with a CPT expert. Each call includes discussions of the CPT protocol, challenging cases, treatment obstacles, and specific issues raised by participants within each group. Both tele-consultation conditions include a maximum of six to eight clinicians per call. CPT experts provide consultation across both consultation conditions to control for any expert-related effects. The prescribed and proscribed activities for each consultation condition are described in manuals, and study team members ([name], [name], ML) review consultant calls on a monthly basis to ensure that fidelity to the consultation condition is maintained. Consultants are trained by study team members prior to beginning consultation calls and receive consultation and feedback every four to six weeks or as needed for the first two waves of consultation, and as needed during the third consultation wave.

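### The monitoring-only arm cannot formally test whether recording and fidelity review raise fidelity, because all three arms are recorded and rated

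*Protocol article*

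**What the plan says.** The second innovation listed in the Discussion of the protocol article says that including the monitoring-only arm makes it possible to test an unevaluated strategy for raising fidelity, namely recording sessions under known review. The next sentence adds: "Our control condition allows for the formal testing of this possibility". The second half of that sentence gives the arm another purpose, to show what expert consultation adds.

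The rest of the article describes what each arm receives:

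- Methods, on the arms: "The conditions are: standard group tele-consultation, technology-enhanced group tele-consultation, or no consultation/fidelity monitoring only".
- Methods, on recording: participation "requires that all clinicians consent at least two clients to have all of their CPT sessions audio-recorded for use in consultation and/or fidelity rating".
- Methods, on rating, with no restriction by arm: "Four therapy sessions will be randomly selected across the six-month period for fidelity rating".
- Interventions, on the incentive, open to everyone who uploads the required material: "Provider status will be awarded to clinicians who demonstrate an acceptable level of fidelity to CPT based on session recordings randomly selected" from the end of the support period.
- Recruitment and randomization: clinicians began recording once back at their workplaces after the workshop.
- Trial status: a high proportion of clinicians uploaded recordings at baseline and during the consultation period.

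None of the three hypotheses under Research questions and hypotheses concerns an effect of monitoring.

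**The concern.** To test whether monitoring raises fidelity, monitored clinicians must be compared with clinicians who are not monitored, or the same clinicians must be observed before monitoring began. The article describes neither. Recording, rating and the fidelity-based credential apply in every arm, and the earliest recordings are already study recordings.

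The Discussion presents this comparison as part of a major advance and expects the results to inform policy on post-workshop support. If the sentence stands, good or rising fidelity in the monitoring-only arm could be taken as a tested result in favour of recording and rating. The same pattern could come from the workshop, from practice with CPT, from the passage of time, or from the sort of clinician who volunteers. A health system could then adopt monitoring on evidence that this trial cannot supply.

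**Working it through.** The plan gives no figure for a monitoring effect, so there is none to reproduce. The question is which effects the three arms can estimate.

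**Step 1: what each arm contains.** From Methods and Interventions, coding monitored / consultation / technology:

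- Monitoring only: 1, 0, 0
- Standard tele-consultation: 1, 1, 0
- Technology-enhanced tele-consultation: 1, 1, 1

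**Step 2: estimability.** With an intercept added, the rows of the design matrix are (1,1,0,0), (1,1,1,0) and (1,1,1,1). The monitored column is identical to the intercept. The rank is 3 for 4 parameters. An effect is estimable only if adding its contrast as a row leaves the rank unchanged:

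- Monitoring, (0,1,0,0): rank rises, not estimable.
- Consultation, (0,0,1,0): rank unchanged, estimable.
- Added technology, (0,0,0,1): rank unchanged, estimable.

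Adding an unmonitored arm, (1,0,0,0), raises the rank to 4 and makes the monitoring effect estimable. Without such a comparator, no number of clinicians does.

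**Step 3: monitoring effects that differ by arm.** Let monitoring add a, b and c in the three arms, let consultation add k, technology add t, and let u be mean fidelity after the workshop without monitoring. The arm means are u + a, u + k + b and u + k + t + c. The differences between successive arms are k + (b − a) and t + (c − b). None of a, b or c can be recovered: u + a appears only as a sum, and b − a and c − b appear only mixed with k and t. The conclusion therefore does not need an equal effect in every arm. With unequal effects, k and t in Step 2 are read as what consultation and technology add in clinicians who are already monitored. The trial estimates those quantities.

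**Step 4: the baseline recordings.** Trial status reports uploads at baseline. These were made by enrolled clinicians for the study, and Recruitment and randomization places the start of recording after the workshop. They allow change over time to be described within the monitoring-only arm, but every point on that trend is monitored, and time and practice change along with it.

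**Step 5: the indirect route through a null result.** Could similar fidelity in the control and consultation arms be taken as a sign that monitoring works? Using the inputs under Sample size (30 clinicians per arm, 4 rated sessions, within-provider correlation 0.38), and assuming a normal approximation on clinician means with no separate agency term:

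- Variance factor: (1 + 3 × 0.38) / 4 = 0.535
- Standard error of a pairwise difference: √(2 × 0.535 / 30) = 0.189 SD
- Half-width of the 95% confidence interval: 1.96 × 0.189 = 0.37 SD
- Difference detectable with 80% power: (1.96 + 0.84) × 0.189 = 0.53 SD, within the plan's stated range of 0.41 to 0.55

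A non-significant pairwise difference would still leave room for a sizeable consultation effect. Even exact equality would show only that consultation added nothing to monitoring, not that monitoring itself did anything.

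**The case against.** The strongest reply is that this is one sentence in a Discussion. No hypothesis, sample size assumption or analysis in the article rests on it. The Background states the control arm's purpose correctly, as measuring what consultation adds, and the second half of the disputed sentence repeats this. Testing a potentially efficient strategy could also be read as comparing a cheap option with two dearer ones, which the design does allow.

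The point about weight stands and lowers the severity. The milder reading is only partly available, because the Discussion names the strategy as one for increasing fidelity, and that needs a comparison without it. Nor can the matter be left to an analysis plan, since no analysis can estimate the effect of an exposure that every clinician has.

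A reader might go further in three ways that the documents do not support:

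- **That monitoring shifts all arms equally and so leaves every between-arm difference unchanged.** This assumes an equal, additive effect. In the technology-enhanced arm, the expert and group members also listen to recordings, so the experience of being reviewed is not the same across arms. Step 3 does without the assumption.
- **That the abstract misdescribes the control.** The abstract does set consultation against clinicians with no formal support (clinicians are to "have improved patient outcomes compared with clinicians receiving no formal post-workshop support"), but its next sentence names the third arm as fidelity assessment without consultation. Background, Methods and Discussion also call the arm fidelity monitoring only.
- **That recording always followed allocation.** The article says recording began on return to the workplace and that allocation was notified within a week of the workshop. It does not fix the order of the two.

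**Conclusion.** The Discussion attributes to the design a property it does not have. The effect of recording under known review is not estimable from this trial: none of the three pairwise comparisons isolates it, and the baseline recordings supply no unmonitored reference. This rests on one reading of Methods and Interventions, that recording, rating and eligibility for Provider status apply in all arms, which the text states without exception.

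Severity is minor to moderate. A reader might infer that the primary comparison is compromised. It is not: the randomised contrasts among the three arms remain valid, provided they are read as what consultation adds to workshop plus fidelity monitoring. What the trial loses is any conclusion about whether monitoring itself raises fidelity.

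**What to change.** In the Discussion of the protocol article:

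- Delete the claim of formal testing, and the matching statement in the preceding sentence that including the monitoring-only arm permits a test of the strategy.
- State that the trial estimates the increment in fidelity from standard and from technology-enhanced consultation over workshop plus fidelity monitoring.
- State that fidelity levels or trends within the monitoring-only arm are descriptive and are not evidence that monitoring raises fidelity.

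Optionally, align the abstract's opening description of the comparator with the arm name in its next sentence.

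The cost is wording only. Data collection, sample size and the primary analysis do not change, and the sponsor gives up only a claim that the design cannot support. If a test of monitoring is wanted, it needs an unmonitored comparator in a separate study.
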